**Standard procedures**																	
***Review medical history***		X		X^a^	X	X	X	X	X	X	X	X	X	X	X	X	
***Offer contraception***	X	X		X^a^	X	X	X	X	X	X	X	X	X	X	X	X	X
**Offer PrEP**	X	X		X^a^	X	X	X	X	X	X	X	X	X	X	X	X	X
***Record AE/SAE***	X	X		X^a^	X	X	X	X	X	X	X	X	X	X	X	X	X

**Fig. 1 Fig1:**
[figure not shown]
Participant enrollment, intervention, and assessment

## Sample size {14}

### Aims 1 and 2

#### Assumptions

Based on prospective data on HPV epidemiology in Africa, we anticipate 70% of young, sexually active women in Kenya will be HPV 16/18/31/33/45/52/58 naïve (as documented by baseline serology and HPV DNA) and eligible to contribute to an incident persistent HPV 16/18 and HPV 16/18/31/33/45/52/58 outcome. We assume the incidence of persistent HPV 16/18 to be 5 per 100 person-years and the incidence of persistent HPV 16/18/31/33/45/52/58 to be at least 5 per 100 person-years. We expect the efficacy of the bivalent and nonavalent vaccines to be 75% to prevent incident persistent HPV 16/18 infection due to lower geometric mean titers in observational data following single-dose versus three-dose vaccination [10]. To estimate the sample size, we assumed fixed follow-up time, i.e., all persons are followed for the same length of time, and loss-to-follow-up of 10%. The sample size estimate is based on a fixed number of events and the Hazard Ratio models (SeqDesign in R). For the null hypothesis, the HR = 1.0 and for the alternative hypothesis the HR = 0.25.

#### Total sample size

Accounting for women who are HPV 16/18 DNA-positive or seropositive at baseline, we estimate that 2250 young women age 15–20 years would need to be enrolled (750 participants per arm). We estimated, with a 3:1 screening to enrollment ratio, approximately 9000 young women will be screened to identify 2250 eligible participants.

#### Power

Accounting for 30% prevalent HPV infections at baseline and month 3, 10% loss-to-follow-up (LTFU), and 1-year fixed follow-up time after accrual, we have 90% power to see a 75% reduction in persistent infections between either of the two immediate HPV vaccine arms and the delayed HPV vaccination (Table 2, which shows the average number of events per arm). Assuming an additional 18% prevalent infections at month 3 for a total of 48% prevalent infections excluded at baseline and month 3, 10% LTFU, and 1-year fixed follow-up time after accrual, we have 80% power to see a 75% reduction in persistent incident infections between the immediate and the delayed vaccine arms.

**Table 2 Tab2:** DSMB recommendations

Primary data analysis recommendation	Communication strategy probable components
1. That the study continues as planned.	Routine action indicated • Routine communication to PIs and critical collaborators • Distribution of primary data analysis minutes to relevant parties
2. That the study be modified because policy changes now recommend single-dose vaccination. 3. That the study be stopped due to concerns about participant safety, including social harms.	Urgent action indicated • Expedited communication to PIs, critical collaborators, regulators, and associates • Key messages and briefing materials • Protocol modifications • Participant information • IRB and regulatory approvals • Distribution materials to relevant organizations

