#### Adjusting the timing of the primary analysis to ensure adequate power for the analysis

If the coronavirus disease (COVID-19) pandemic delays follow-up, the primary analysis could be delayed to allow sufficient endpoints and adequate power for the primary analysis.

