## Data collection and management

### Plans for assessment and collection of outcomes {18a}

#### Follow-up procedures

Participants complete a questionnaire on clinical history including adverse events, symptoms of sexually transmitted infections (STIs), exposure and sexual behavior, clinical health, updated contact information, and adherence to SRH services. A limited physical exam and pelvic examination for specimen collection is conducted every 6 months. Providers conduct visual inspection for genital warts and a speculum examination to collect a lateral vaginal swab and cervical swab for HPV DNA testing and specimens for STI testing. The procedures for the pelvic and speculum exams are explained to the participants, questions answered. If a participant declines pelvic examination, they are given the option to self-collect a vaginal swab.

Specimens for HPV DNA testing are collected by clinicians every 6 months. An additional swab is self-collected by the participant at month 3 for HPV DNA testing.

Serum is collected for HPV 6/11/16/18/31/33/45/52/58 serologic testing at enrollment, month 18 and month 36 for all participants and at month 1 and month 24 for the 900 immunobridging sub-study participants to test the immunologic response to the vaccines, as part of the immunobridging sub-study described below.

Sixty participants, consecutive participants at month 1, and 40 participants at months 36 and 37 will have ~ 20–40 mL of blood collected for B cell immunologic testing, to determine if the vaccine establishes long-term memory for neutralizing HPV infections. Once training for the B cell substudy is complete, enrollment of consecutive participants begins.

As part of comprehensive SRH services, contraception; STI, HIV, and pregnancy testing; and PrEP will be offered to participants every 3 months. Participants with new medical concerns will be referred for care as appropriate.

In response to the COVID-19 pandemic, telehealth visits were introduced for follow-up visits at months 9, 15, 21, and 27 to complete visit questionnaires. For visits with cervical swab collection, months 6, 12, 18, and 24, participants were also given the option to have the swab collected at a near-by facility or self-collect the swab for collection by courier. Contraception and PrEP delivery were also available by courier.

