### Outcome

Outcome is as follows: Persistent HPV, defined as vaccine type specific HPV detected at two consecutive time points no less than 4 months apart after month 3 and up to and including 18 months apart (same HPV type at each time point) in the first 18 months post-randomization.

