### Definition of endpoints

The persistent HPV endpoints (16/18 and 16/18/31/33/45/52/58) are defined in participants who experience the outcome defined above as the time from the month 3 visit to first detection of vaccine type specific HPV.

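### The stated 90%/80% power assumes one year of follow-up, but on schedule the month-18 endpoint can confirm only infections first detected over a nominal nine months (months 3 to 12)

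*Protocol article*

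**What the plan says.** The Power section of the protocol article gives "1-year fixed follow-up time after accrual, we have 90% power to see a 75% reduction in persistent infections" after removing 30% of women as prevalent infections and 10% as lost. With 48% removed it gives 80%. For expected events it points to "Table 2, which shows the average number of events per arm". The Assumptions section adds: "We assume the incidence of persistent HPV 16/18 to be 5 per 100 person-years", a hazard ratio of 0.25, and a design based on a fixed number of events.

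The endpoint is built elsewhere:

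- **Modified intent to treat cohort:** women who are HPV DNA positive at enrolment or month 3 are excluded.
- **Outcome:** the same type must be found at two consecutive time points, at least 4 months apart, after month 3 and "in the first 18 months post-randomization".
- **Definition of endpoints:** event time is defined "as the time from the month 3 visit to first detection of vaccine type specific HPV".
- **Follow-up procedures and Table 1:** "Specimens for HPV DNA testing are collected by clinicians every 6 months", so swabs after month 3 and up to the primary analysis fall at months 6, 12 and 18.

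If COVID-19 delays follow-up, "the primary analysis could be delayed to allow sufficient endpoints and adequate power for the primary analysis".

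**The concern.** Put together, these rules leave an infection first detected at the month-18 swab with no confirming swab inside the window. Countable infections are those first detected at month 6 or month 12, which on schedule means those acquired between months 3 and 12. That is 0.75 year, not the one year in the power statement. Nothing in the article reconciles the two.

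What is at stake is the power of the primary analysis, above all in the 48%-excluded scenario, where the plan already has only 80%. A reader cannot find the mismatch from the event counts, because the Table 2 cited for them contains the DSMB recommendations.

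**Working it through.** **Inputs.** 750 per arm (Total sample size); 5 per 100 person-years in controls and hazard ratio 0.25 (Assumptions); 30% or 48% excluded and 10% lost (Power). Alpha is not stated for the primary comparison; two-sided 5% is assumed.

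Evaluable women per arm: 750 × 0.70 × 0.90 = 472.5 and 750 × 0.52 × 0.90 = 351.

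**Formulas.** For a window of T years, control events = n × 0.05 × T, vaccine events = one quarter of that, and D is their sum. Freedman power = Φ(√D × (1 − 0.25)/(1 + 0.25) − 1.96) = Φ(0.6√D − 1.96).

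**Step 1: reproduce the plan (T = 1).**

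- 30% excluded: 23.6 + 5.9 = 29.5 events; Φ(0.6 × 5.434 − 1.96) = Φ(1.30) = 90.3%.
- 48% excluded: 17.6 + 4.4 = 21.9 events; Φ(0.6 × 4.684 − 1.96) = Φ(0.85) = 80.2%.

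A two-proportion comparison with event probabilities 1 − exp(−rate × T) gives 90.2% and 80.0%. Both methods match the stated 90% and 80%.

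**Step 2: the window that the endpoint allows (T = 0.75).**

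- 30% excluded: 17.7 + 4.4 = 22.1 events; Φ(0.6 × 4.706 − 1.96) = Φ(0.86) = 80.6%.
- 48% excluded: 13.2 + 3.3 = 16.5 events; Φ(0.6 × 4.056 − 1.96) = Φ(0.47) = 68.2%.

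The two-proportion version gives 80.4% and 68.0%, with 17.4 vs 4.4 and 12.9 vs 3.3 events.

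**Step 3: check with the planned type of test.** A log-rank test was simulated without site strata (20,000 runs). At one year power was about 93% and 83%. At nine months, with detection at months 6 and 12, it was about 83% and 71%.

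**Step 4: sensitivity to what the article leaves open.**

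| Reading | Window (years) | Freedman power, 30% / 48% excluded |
|---|---|---|
| As stated in the Power section | 1.00 | 90.3% / 80.2% |
| On-schedule endpoint, months 3–12 | 0.75 | 80.6% / 68.2% |
| Month-12 visits as late as month 14, still 4 months before month 18 | 0.92 | 87.7% / 76.8% |
| 5 per 100 is the rate over month 3–18 person-time | 1.25 | 95.4% / 88.1% |

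Keeping the planned number of events over nine months would need an incidence of 5/0.75 ≈ 6.7 per 100 person-years.

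**The case against.** The strongest reply is that the size of the shortfall depends on things the article does not fix.

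- **Meaning of the rate.** The primary outcome is an incidence per 100 women-years at risk, and time at risk runs from month 3 to the last negative test by month 18. If 5 per 100 is that rate, 15 months of person-time give about 95% and 88%, and there is no shortfall. This stands as a possible reading. It still does not match the one year in the power statement.
- **Formula.** The Schoenfeld formula, Φ(√(D/4) × |ln 0.25| − 1.96), gives 90.4% and 80.3% at nine months. The designers may therefore have used nine months and written one year. In that case the text is wrong. The simulated log-rank test at nine months still gives only about 83% and 71%, because Schoenfeld is optimistic at so strong an effect with about 20 events.
- **Exclusions.** The 70% naïve share in Assumptions refers to all seven types, so the share naïve to HPV 16/18 alone is at least that. With an assumed 80–90% naïve, nine months gives about 86–89% (Freedman). The calculation above uses the exclusions that the Power section states.
- **Wording of the outcome.** The Outcome section lets the two positives be up to 18 months apart, yet two positives after month 3 and by month 18 can be at most 15 months apart. This leaves some doubt whether confirmation must fall by month 18. The censoring rule, and the Durability analysis section, which moves the outcome limit from 18 to 36 months, both support month 18 as the limit.

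A reader might also infer that the COVID-19 delay clause adds no endpoints. The article does not support that: waiting lets late participants complete their month-12 and month-18 tests. What a delay cannot do is move the month-18 limit.

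**Conclusion.** The mismatch is real: one year is assumed, while the endpoint on schedule confirms infections from a nominal nine months. If 5 per 100 person-years is the acquisition rate of infections that go on to persist, power for HPV 16/18 with the stated exclusions is about 80–83% rather than 90%, and about 68–71% rather than 80%. Expected events are about 17 vs 4 and 13 vs 3 per arm. This also assumes two-sided 5%, a constant rate, confirmation at the next visit and losses removed at the start.

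A reader might conclude that the trial's power simply is 80% and 68%. The article does not support so firm a figure. Late month-12 visits could bring it to at most about 88% and 77%, and the other reading of the rate gives about 95% and 88%. For the seven-type endpoint, whose incidence is assumed to be 5 or more, the nine-month figures are a lower bound. The month-36 analysis is not affected.

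**What to change.** In the Power section, replace the one-year basis with the window that the endpoint allows, and restate power as about 80–83% (30% excluded) and 68–71% (48% excluded). State whether 5 per 100 person-years is an acquisition rate or a rate over month 3–18 person-time, and revise the figures if it is the latter. Give alpha, the formula used and the expected events per arm, and correct the Table 2 citation. In the section on delaying the analysis, say that a delay recovers late tests but does not extend the month-18 limit. The cost is text only, and possibly a less favourable figure.

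Optionally, by approved amendment before unblinding, add an analysis in which an infection first detected by month 18 may be confirmed at the month-24 swab that Table 1 already schedules. Under the acquisition-rate reading this widens the window to 15 months (29.5 vs 7.4 and 21.9 vs 5.5 events; about 95% and 88%). It needs no new visits, but it does need IRB and regulatory approval and a later database lock. Recruitment closed on 15 November 2019, so the last nominal month-24 visit is about November 2021. That leaves little time before the planned Q1 2022 primary results, and less if COVID-19 restrictions moved visits.

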#### Adjusting the timing of the primary analysis to ensure adequate power for the analysis

If the coronavirus disease (COVID-19) pandemic delays follow-up, the primary analysis could be delayed to allow sufficient endpoints and adequate power for the primary analysis.

## Recruitment {15}

### Strategies for recruitment

The study sites have experience recruiting young women for intervention studies including HPV vaccine studies, pre-exposure prophylaxis (PrEP) for HIV prevention studies, and sexually transmitted infection studies. We engage key stakeholders including cervical cancer prevention advocacy groups, non-governmental organizations, and local and national Ministry of Health staff. Study teams use informal baseline surveys at local training centers, clinics, non-governmental organizations, and colleges to identify where the study population will be recruited. Each site also identifies and analyzes the stakeholders in terms of their influence, level, and engagement mechanism. Using this information, the teams construct map recruitment areas. Recruitment approaches include the following strategies: engagement with identified health facilities or learning facilities attended by adolescents and young women, working with enrolled participants to identify and refer their peers who may be interested for further information (respondent driven sampling recruitment techniques), and conceptualize general messages into a drama for local radio stations to create awareness on HPV and the need for cervical cancer screening. Other strategies include the use of mobilizers, mission/community theatre recruitments, cervical cancer screening campaigns, and use of technology such as phones and tablets for information and education (edutainment) to maximize recruitment. The stakeholder information analysis is used to design community entry, mobilization, and engagement. All study related recruitment materials have regulatory approval.

## Assignment of interventions: allocation

### Sequence generation {16a}

#### Randomization procedures

The randomization allocation lists are generated using computer-generated random numbers to create blocked randomization, stratified by site. A 1:1:1 random allocation to the three arms of the trial was used. Randomization is blocked to ensure balance between the arms and stratified by site to account for potential different risks of incident persistent HPV infection. The randomization is designed by a study statistician or designee. A copy of the code used to generate the randomization, the block size used, and the randomization list itself are stored in a secure directory, to which only unblinded members of the KEN SHE statistical team have access.

## Concealment mechanism {16b}

Blinded study assignment is implemented via http://www.randomize.net, or when necessary due to lack of internet, using a back-up envelope system. The randomization arm is not determined until the participant has completed all screening procedures (above).

### Randomize.net

Unblinded members of the statistical team generated the allocation order for randomization and provided separate allocation lists to Randomize.net, as well valid participant IDs (PTIDs).

The randomization sequence is implemented in sequential order for each site. Unblinded site pharmacy staff enter the PTID on Randomize.net, the PTID is verified through Randomize.net, and the next sequential treatment arm is assigned. The date of randomization and the blinded “randomization ID” are witnessed on site and are recorded on the study source documentation and study case report form.

### Back-up randomization envelopes

A limited number of envelopes (*n* = 30 per site) are provided to sites for use in randomization allocation in the case of power or internet outage where the site is unable to access Randomize.net using a computer or a mobile phone. To create the back-up envelopes, additional blocks of randomization assignment were generated by the KEN SHE statistical team, and printouts that detail envelope number, randomized vaccine, and blinded randomization ID were inserted into each of 30 envelopes, with the sequence number on the printout matching that on the envelope. Envelopes are delivered to the sites at Site Activation Training.

### Vaccine masking

The study participants, investigators, site personnel, the laboratory staff conducting HPV typing of clinical samples by serology and PCR, and the laboratory staff who read and issue diagnoses of Pap tests are blinded to the vaccination group assignments of the subjects for the duration of the study. The site pharmacist is unblinded to the randomization arm and uses Randomize.net to obtain the study group, record the PID and randomization ID on a CRF, and draw up the vaccination for administration. The vaccine volumes are identical (0.5 ml), and the syringes appear identical. The syringe markings are concealed with opaque labels or tape and the syringe is labeled with the PID. The vaccine is administered after the PID is confirmed.

### Implementation {16c}

The enrolment visits is conducted by a blinded KEN SHE study team member.

### Randomization

Participants are randomly assigned 1:1:1 to immediate single-dose bivalent or nonavalent HPV vaccine (and delayed meningococcal vaccine) or delayed nonavalent HPV vaccine (and immediate meningococcal vaccine) by the unblinded study pharmacist, using the web-based randomization software.

### Vaccination

The vaccine information (lot number and expiry date) is recorded on pharmacy logs by the unblinded study pharmacist. The unblinded pharmacist accesses the web-based randomization or opens the randomization envelope in the numbered sequence and records the PID and blinded randomization ID on a CRF. The pharmacist is responsible for vaccine inventory and accounting, including vaccine that is not used, for example, if the dose is broken. Vaccines will be stored under appropriate controlled conditions with regulated access.

### End of the enrolment visit

At the end of the enrolment visit, an appointment is made at month 1 for substudy participants, and at month 3 for all participants. The first 900 participants were included in the immunobridging substudy. Staff provide information on adverse events associated with vaccination, ensured participants have contact information for the study team, and answer participant questions.

## Assignment of interventions: blinding

### Who will be blinded {17a}

The study participants, investigators, site personnel, the laboratory staff conducting HPV typing of clinical samples by serology and PCR, and the laboratory staff who read and issue diagnoses of Pap tests are blinded to the vaccination group assignments of the subjects for the duration of the study.

### Procedure for unblinding if needed {17b}

Participants may be unblinded in consultation with the Country Medical Director and Principal Investigators for clinical reasons. Participant may choose to be vaccinated outside the trial and continue follow-up in the study.

## Data collection and management

### Plans for assessment and collection of outcomes {18a}

#### Follow-up procedures

Participants complete a questionnaire on clinical history including adverse events, symptoms of sexually transmitted infections (STIs), exposure and sexual behavior, clinical health, updated contact information, and adherence to SRH services. A limited physical exam and pelvic examination for specimen collection is conducted every 6 months. Providers conduct visual inspection for genital warts and a speculum examination to collect a lateral vaginal swab and cervical swab for HPV DNA testing and specimens for STI testing. The procedures for the pelvic and speculum exams are explained to the participants, questions answered. If a participant declines pelvic examination, they are given the option to self-collect a vaginal swab.

Specimens for HPV DNA testing are collected by clinicians every 6 months. An additional swab is self-collected by the participant at month 3 for HPV DNA testing.

Serum is collected for HPV 6/11/16/18/31/33/45/52/58 serologic testing at enrollment, month 18 and month 36 for all participants and at month 1 and month 24 for the 900 immunobridging sub-study participants to test the immunologic response to the vaccines, as part of the immunobridging sub-study described below.

Sixty participants, consecutive participants at month 1, and 40 participants at months 36 and 37 will have ~ 20–40 mL of blood collected for B cell immunologic testing, to determine if the vaccine establishes long-term memory for neutralizing HPV infections. Once training for the B cell substudy is complete, enrollment of consecutive participants begins.

As part of comprehensive SRH services, contraception; STI, HIV, and pregnancy testing; and PrEP will be offered to participants every 3 months. Participants with new medical concerns will be referred for care as appropriate.

In response to the COVID-19 pandemic, telehealth visits were introduced for follow-up visits at months 9, 15, 21, and 27 to complete visit questionnaires. For visits with cervical swab collection, months 6, 12, 18, and 24, participants were also given the option to have the swab collected at a near-by facility or self-collect the swab for collection by courier. Contraception and PrEP delivery were also available by courier.

